#### Criteria for inclusion/exclusion

Inclusion criteria are: women and men; 18–65 years of age; presence of MDD according to ICD-10 diagnostic criteria (F31 type II, F32, F33); BDI ≥ 17 (at least borderline clinical depression); currently not meeting the ACSM physical activity recommendations (IPAQ < 150 min/week of moderate-to-vigorous physical activity); written informed consent; and ability to speak and read German.

Exclusion criteria are: presence of history of bipolar disorder type I (F31 type I), history of schizophrenia, or schizoaffective disorder; current active alcohol or drug abuse or dependence; any significant medical condition that contraindicates safe participation in physical activity; active suicidal intent; evidence of significant cardiovascular, neuromuscular, or endocrine disorders limiting regular physical activity as per ACSM absolute contraindications to exercise (including a recent significant change in the resting ECG suggesting significant ischaemia, recent myocardial infarction or other acute cardiac event, unstable angina, uncontrolled cardiac dysrhythmias causing symptoms or haemodynamic compromise, symptomatic severe aortic stenosis, uncontrolled symptomatic heart failure, acute pulmonary embolus or pulmonary infarction, acute myocarditis or pericarditis, and suspected or known dissecting aneurysms) or medical contraindications to physical activity indicated by the Physical Activity Readiness Questionnaire (PAR-Q) [100]; and inability to speak and read German.

#### Healthy controls

To compare baseline differences in the primary and secondary outcome(s) between patients and healthy controls, an age- and gender-matched sample of 167 participants will be recruited through advertisements in newspapers and through word-of-mouth recommendation. Inclusion criteria for healthy controls are: women and men; 18–65 years of age; HAMD17 ≤ 7; BDI ≤ 13; currently not meeting the ACSM physical activity recommendations (IPAQ < 150 min/week of moderate-to-vigorous physical activity); written informed consent; and ability to speak and read German.

### Procedures

#### Data assessment

Screening will take place in the first week after admission to in-patient treatment. Identical data assessment will take place 2–3 weeks after admission to in-patient treatment (baseline), and 6 weeks (post) and 12 months (follow-up) after discharge from in-patient treatment. The primary outcome is objectively assessed physical activity (Actigraph wGT3x-BT monitor, 7 days). Secondary outcomes are self-reported physical activity, cardiorespiratory fitness, autonomic function cognitive and social determinants of exercise, depression severity, self-perceived physical and psychological health, insomnia symptoms, cognitive function, cardiovascular health risk markers, and biomarkers of MDD. Moreover, the serotonin transporter (5-HTT) polymorphic promoter region (5-HTTLPR) is assessed as a potential moderator of intervention effects [21]. More information regarding the various instruments is presented in the following.

### Intervention and placebo control condition

Patients assigned to the IG or the PCG receive treatment as usual from their psychiatrists according to the Swiss treatment guidelines for major depression [101]. Moreover, patients from both groups continue the therapy provided by their practitioner and therapist for their depression (i.e. psychotherapy, use of antidepressants).

#### Intervention programme: individually tailored physical activity promotion

Patients assigned to the IG will receive an individually tailored physical activity counselling to provide support and encouragement to increase physical activity. Two face-to-face meetings will take place during the clinical treatment which lasts between 6 and 8 weeks on average. The meetings will take place approximately in weeks 4 and 6 of in-patient treatment. The same physical activity facilitator will develop a physical activity plan with the participant, tailored to the individual’s current activity levels, activity type, and intensity preferences, and will promote behavioural change techniques which have been proven effective in previous studies [102–107]. Additionally, starting 1 week after discharge from in-patient treatment, patients of the IG will receive bi-weekly telephone counselling and SMS prompts until 12 months after discharge. Telephone counselling and push notifications will help to ensure adherence of patients to their physical activity and exercise plans/prescription, or facilitate the adaptation of these plans. Furthermore, a smartphone app will be developed which can be used to support patients in their planning and self-monitoring of physical activity and exercise behaviour.

Exercise prescriptions follow the standards of the American College of Sports Medicine [90, 91], stating that individuals should engage in at least 30 min of moderate-intensity physical activity on 5 days per week, or 20 min of vigorous-intensity aerobic exercise on 3 days each week. A variety of activities such as aerobic exercise, resistance exercise, multi-modal group-based exercise, daily physical activity (e.g. walk or take bike for grocery shopping), and so forth, will be advised.

The intervention builds on a standardized, theory-based, short, low-cost lifestyle physical activity counselling programme, which was specifically designed for an in-patient rehabilitation setting (MoVo-Lisa = Motivation, Volition and Lifestyle-integrated Sport Activity). It consists of two individual (face-to-face) counselling sessions and an extended counselling session via telephone after discharge from the clinic. The first session (60–75 min) will take place 1 week after the baseline data assessment. The second session (45–60 min) will take place 1 week before the end of in-patient treatment. The third session (75–90 min) will take place 1–2 weeks after discharge from in-patient treatment via telephone to give patients the possibility to test their physical activity plans in their familiar environment, and to allow the identification of real-life physical activity obstacles.

All sessions aim at promoting motivational and volitional strategies to foster long-term behavioural change. Following Michie et al.’s [102] behaviour change taxonomy, motivational strategies include: clarification of personal health objectives (*goal setting [outcome]*, V1: 1.3); contemplation of different actions to achieve the health objectives (*goal setting [behaviour]*, V1: 1.1); reflection of pros and cons associated with the new behaviour (*pros and cons*, V1: 9.2); checking self-concordance of these goals (*review behaviour/outcome goals*, V1: 1.5/1.7); and reflection of outcome experiences (*monitoring of emotional consequences*, V1: 5.4). Volitional strategies include: generation of implementation intentions (*action planning*, V1:1.4); anticipating personal barriers (*problem-solving*, V1:1.2); developing counter strategies (*restructuring of the physical/social environment*, V1:12.1/12.2); contracting (*behavioural contract*, V1:1.8); mobilization of social support (*social support*, V1:3); and self-monitoring the new behaviour (*self-monitoring of the behaviour and outcomes of the behaviour*, V1:2.3/2.4). The intervention will be designed to match the specific stage of depression. Facilitators will focus on pessimistic beliefs such as negative outcome expectations and self-efficacy, as well as planning deficits linked with depression [108]. Recently, reviewers identified losing weight (83% of patients), improving mood (81%), and reducing stress (78%) as the most relevant motives for exercise in patients with severe mental illnesses, whereas low mood and stress (61%) and lack of social support (50%) turned out to be the most relevant exercise barriers [69]. Physical activity facilitators will place a special emphasis on these motives and barriers when developing physical activity promotion strategies.

#### Administration of experimental intervention

The aim is to have at least two face-to-face individual counselling sessions, have 26 follow-up telephone contacts (on a bi-weekly basis), and send 52 message prompts by the 12-month time point. Telephone contacts will be used to discuss problem-solving around barriers, reinforce progress towards behaviour change, and adapt initial goals and plans. Moreover, follow-up contacts serve to strengthen relapse strategies so that patients understand that relapses are common during behaviour change, and that dysfunctional cognitions, emotion, and behaviours can jeopardize maintenance of a physically active lifestyle [33].

#### Smartphone application

A smartphone app will support patients in their planning and self-monitoring of physical activity and exercise behaviour. This newly developed app designed for online coaching will serve as a tool for communication, exchange of weekly activity plans, and documentation of physical activity. Via the app, the physical activity facilitator can assist the participant in developing physical activity plans and can access the self-monitoring data. Both participants and physical activity facilitators can access and modify the physical activity plans online.

Adherence to the intervention protocol will be monitored by the physical activity facilitators. A thorough documentation of the physical activity facilitator’s work with the participant will ensure that the adherence to the protocol will be visible. Bi-weekly meetings with the physical activity facilitators and the study team will allow for continued training and minimize differences in the delivery of the intervention between facilitators and within facilitators over time.

#### Placebo control condition

One week after the baseline assessment, in addition to treatment as usual, patients assigned to the PCG will receive written information about health-enhancing physical activity based on the “Core document for Switzerland” published by the Federal Office of Sport (BASPO) in collaboration with other institutions. This document summarizes the current knowledge in relation to health-enhancing physical activity. The patients will obtain information about the following topics: why is physical activity healthy; what are the minimal physical activity recommendations; how physically active are people in Switzerland; and what are the costs of physical inactivity?

One week before the end of the in-patient treatment, patients will meet the physical activity facilitator. The facilitator will summarize the key contents of the “core document” by showing a short animation film (https://www.youtube.com/watch?v=zNZenOnGI0U) and discuss questions with the patient. The control condition is not intended as a bona fide intervention [109, 110] and an active therapy, but to control for placebo effects of the intervention condition.

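### The control condition ends before discharge, so it does not control for placebo effects of post-discharge coaching on depression, stress, sleep and self-rated health

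*Protocol article*

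**What the plan says.** The protocol article calls the comparator a placebo control group in the abstract and under Study design. The section Placebo control condition gives its purpose: it is not meant as a bona fide or active therapy, "but to control for placebo effects of the intervention condition".

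That section describes two components. One week after baseline, "patients assigned to the PCG will receive written information about health-enhancing physical activity". Later, "One week before the end of the in-patient treatment, patients will meet the physical activity facilitator", who shows a short film and answers questions. It describes nothing after discharge.

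For the intervention group (IG), the section Intervention programme describes two face-to-face sessions in the clinic and a further session after it: "The third session (75–90 min) will take place 1–2 weeks after discharge from in-patient treatment via telephone". It also states that "patients of the IG will receive bi-weekly telephone counselling and SMS prompts until 12 months after discharge". Under Administration of experimental intervention, the target is at least two face-to-face sessions and to "have 26 follow-up telephone contacts (on a bi-weekly basis), and send 52 message prompts by the 12-month time point". An app links patient and facilitator as well.

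After baseline, outcomes are measured "6 weeks (post) and 12 months (follow-up) after discharge from in-patient treatment" (Data assessment). The secondary outcomes listed there include "depression severity, self-perceived physical and psychological health, insomnia symptoms".

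**The concern.** A control condition accounts for placebo effects to the extent that it reproduces the non-specific parts of the experimental condition, such as attention, support and expectation of benefit, over the period in which outcomes arise. Here both post-baseline assessments fall after the control condition has finished, while coaching is in progress (week 6) or reaching its end (month 12).

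Regular conversations with a facilitator could improve mood, stress, sleep and self-rated health without any change in activity. The intervention's content makes this plausible. Facilitators work on pessimistic beliefs and self-efficacy (Intervention programme), and the calls deal with unhelpful thoughts and emotions (Administration of experimental intervention).

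What is at stake is interpretation. If a depression benefit is reported against a placebo control, readers will take it that non-specific effects were excluded and will credit physical activity. The Discussion points that way when it expects the findings to support exercise as a form of medicine. The Background shows that the comparator matters: it cites a meta-analysis with g = 1.24 against no intervention, 0.68 against control conditions, 0.48 against usual care and 0.22 against psychological interventions. Those figures do not estimate any bias in this trial, but they show why the comparator must be described accurately.

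**Working it through.** **1. Reproduce the planned number of calls.** Calls are bi-weekly and start one week after discharge, so they fall in weeks 1, 3, 5, …, 51. That is (51 − 1)/2 + 1 = 26, which agrees with the protocol's figure.

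**2. Count facilitator contact at each assessment.** The documents do not say whether the 75–90 min telephone session is one of the 26 calls, so both readings are shown. The week-6 prompt count assumes that the 52 prompts are spread evenly: 52 × 6/52 = 6.

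| After discharge, up to | IG calls | IG prompts | Control, as described |
|---|---|---|---|
| 6-week assessment | 3 (weeks 1, 3, 5); 4 if the long session is separate | about 6 | 0 |
| 12-month assessment | 26; 27 if separate | 52 | 0 |

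Prompts are kept apart from calls because a text message is not equivalent to a conversation.

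**3. Whole trial.** Planned personal contacts in the IG are 2 + 26 = 28 (29 if the long session is separate), against 1 described meeting in the control group.

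**4. Contact time, by assumption.** The three structured sessions total 60 + 45 + 75 = 180 min to 75 + 60 + 90 = 225 min. The length of the other calls is not stated. Assume 10–30 min each and that the long session is one of the 26, leaving 25 others:

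- lower end: (180 + 25 × 10)/60 = 430/60 ≈ 7.2 hours
- upper end: (225 + 25 × 30)/60 = 975/60 ≈ 16.3 hours

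The control group has one meeting of unstated length. The conclusion does not depend on this range.

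**5. What both arms share.**

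- Usual psychiatric treatment continues (Intervention and placebo control condition).
- Patients are not told their allocation, and consent is to a test of different ways of promoting activity (Study design).
- The facilitator tells everyone about the clinic's exercise offers, during the in-patient stay.
- Each assessment takes about 2 h and is followed by a personal health profile (Measures).

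Some of these may balance expectancy. None supplies facilitator contact to controls after discharge.

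**6. Compare with the stated purpose.** Facilitator contact in the control arm covers only the in-patient phase, whereas the placebo claim refers to the intervention condition as a whole, most of which takes place after discharge. As described, the claim is not met at week 6 or month 12.

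**The case against.** The strongest reply is that the trial evaluates a counselling programme of which contact is a part. The calls deliver problem-solving, reinforcement, goal adjustment and relapse strategies, which are named techniques rather than idle attention. The purpose section asks how the intervention affects the outcomes against controls, and the primary outcome is accelerometry. No analysis statement says that depression effects will be attributed to activity with non-specific effects ruled out. This stands, and it is why the package comparison is valid.

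It is also fair that the control arm is not left without attention. A reader might infer from the contact counts that controls have no attention or expectation component at all after discharge. The documents do not support that: controls continue usual care, attend the 6-week visit and receive a health profile. Undisclosed allocation, the written material and the facilitator meeting may also balance some in-patient expectancy. What is absent is facilitator contact after discharge.

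A reader might further infer that a full year of unmatched contact lies behind every result. That applies to month 12 only; at week 6 the difference is about 3 calls and some prompts.

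Nor should every psychosocial scale be called a contact artefact. Exercise-related social support is an explicit target of the programme, and its scale asks about help from others such as family and friends.

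Assessor blinding limits rating bias on HAMD17, but it does not remove a real effect of contact on mood. That the control is described as no bona fide therapy does not settle the matter either, because the same sentence goes on to claim placebo control.

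**Conclusion.** The concern holds in a limited form. The stated function of the control condition is not delivered at either post-discharge assessment: 0 facilitator contacts are described for controls, against about 3 calls by week 6 and 26 calls plus 52 prompts by month 12 in the IG. Non-specific effects of that contact on BDI, HAMD17, perceived stress, SF-12 and insomnia are therefore uncontrolled. How large they would be cannot be derived from the documents.

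A reader might go further and conclude that the randomised comparison is invalid or that the primary result is compromised. The documents do not support this. The effect of the whole package against brief information, including on accelerometer-measured activity, can still be estimated. What fails is the placebo-control claim and any inference that separates physical activity from contact.

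This rests on the control condition being fully described in its own section. Figure 1 is not shown, and its caption does not assign the remote telephone counselling to an arm, but the intervention section gives the calls to the IG and the control section mentions none.

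**What to change.** - Describe the comparator as a minimal-information control in place of a placebo control.
- Delete the statement that it controls for placebo effects, or limit it to some balancing of expectancy during the in-patient stay.
- State that the contrast is the whole counselling package, including up to 12 months of facilitator contact, against brief information.
- State that differences in depression, perceived stress, sleep and SF-12 will not be attributed to physical activity itself as opposed to facilitator contact.

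The cost is wording only. Treatment of either arm, the sample size and the assessments stay as they are, so the change can be made although recruitment began in January 2019. The downside is a more modest claim for these secondary outcomes.

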#### Selection, education, and training of the physical activity facilitator

Physical activity counselling will be done by personnel with a background in exercise science and/or psychology, because a majority of patients want professional support when trying to engage in more physical activity [69]. Physical activity facilitators will be trained in behavioural change techniques and coaching through the supervisors. The facilitators will be regularly supervised by the investigators. Knowledge and coaching style of each facilitator will be tested prior to the first coaching session.

#### Participation in physical activity and exercise programmes during in-patient treatment

The physical activity facilitator will inform all participants about the existing exercise activities offered at the clinic. Both groups (IG and PCG) have the possibility to voluntarily participate in these activities.

### Ethical considerations

The proposed research will be carried out in accordance with the ethical principles laid down in the Declaration of Helsinki (1964). Central ethical approval has been confirmed from the “Ethikkommission Nordwest- und Zentralschweiz” (ref. approval no. 2018-00976). Moreover, local ethical approval has been obtained for all study sites. Thus, local ethical approval has been obtained from the “Ethikkommission Nordwest- und Zentralschweiz” for the clinics located in Basel, Riehen, and Solothurn, and from the “Ethikkommission Bern” for the clinic located in Münchenbuchsee. The intervention study was registered in the WHO trial register (trial number ISRCTN10469580). All participants will be informed about the general goals of the study. Informed written consent is required before study entry. Participants are informed that participation in the study is voluntary and that they can withdraw or discontinue at any time without further obligation or potential disadvantages. The participants and outcome assessors are blinded. Medication intake will be recorded as a part of the baseline, post intervention, and follow-up assessments.

After completion of the data assessment, all personal data of the patients will be encoded (each patient will receive a project ID number), so that it will no longer be possible to identify the patients. Data will be entered into an SPSS file. The collected data will be saved digitally. Backup files will be stored regularly on the external cloud *Switchdrive@Universität Basel*. The coding list will be stored in a safe place. Data will only be used for scientific purposes, and will be discarded after completion of the laboratory analyses. Paper records of the study will only be accessible to the main investigators, and will be kept in locked cupboards. After 10 years, all records will be destroyed.

### Measures

The primary outcome, secondary outcomes, moderators, and covariates will be assessed identically at baseline, post intervention, and follow-up by the same examiner at the clinic. As an incentive, healthy controls will receive 50 CHF for their participation in the study. Patients will receive 20 CHF if they participate in the post-intervention and follow-up assessments (as a compensation for their travel expenses). After each data assessment, healthy controls and patients will receive a health profile with information regarding their physical activity and fitness level, blood pressure, blood glucose, blood lipid profile, and body composition. Participants will be instructed to abstain from food and liquids (including coffee and tea) from 22:00 the night before the evaluation for the accurate measurement of blood glucose, blood lipids, and autonomic function. Assessments will last approximately 2 h. The following procedures will be applied by well-trained staff adhering to standardized, quality-controlled protocols.

### Primary outcome

#### Objective physical activity

Objective physical activity will be assessed with an accelerometer (wGT3x-BT; Actigraph, Shalimar, FL, USA) worn around the hip. The devices will be worn during daytime for 7 consecutive days to assess a full weekly period. The sampling epoch will be set at 10 s [111]. Time per day spent in moderate physical activity (MPA; 1952–5723 counts per minute, > 3 MET) and vigorous physical activity (VPA; > 5274 counts per minute, > 6 MET) is determined based on the raw accelerometer counts and the ActiLife® computer software, with cut-off values derived from Freedson et al. [112]. Participants will fill in a non-wear time sheet (e.g. to assess physical activities during which it was not possible to wear the monitor, such as swimming). Physical activities listed on the non-wear time sheet will be included as moderate-to-vigorous physical activities, based on the intensity levels defined in the Physical Activity Compendium [113, 114]. To be included in the data analyses, participants will need at least 5 valid days, including ≥4 valid weekdays and ≥ 1 valid weekend day [115]. Following Herrmann et al. [116], only days with at least 10 h of wear time are considered a valid measure of daily physical activity. The validity of the Actigraph accelerometer device has been documented previously [117]. To the best of our knowledge, no minimal clinically important change (MCID) scores are currently available for physical activity in patients with MDD. The ACSM recommends that individuals should accumulate at least 150 min of moderate-to-vigorous physical activity per week [91]. This is in line with a study by Hoffman et al. [59] showing that in patients with MDD there is a linear increase associated with self-reported exercise regarding the probability of at least partial remission until 150 min of exercise per week, whereas the response curve flattens off beyond this threshold.

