### Participants

#### Recruitment and power calculations

Clinical in-patients aged 18–65 years with a current diagnosis of major depression (ICD-10) will be continuously recruited from the Psychiatric Services Solothurn, Psychiatric Clinics of the University of Basel, Psychiatric Clinic Wyss, Münchenbuchsee, and the Psychiatric Clinic Sonnenhalde, Riehen. In previous studies with non-depressed individuals, individually tailored physical activity promotion was associated with a moderate effect (*d* = 0.50) on the primary outcome (physical activity) [80, 81]. So far, only one study exists examining physical activity counselling among out-patients with depression, yielding an adjusted odds ratios of 2.27 across the 4-month, 8-month, and 12-month follow-up (corresponding *d* = 0.45). Conversely, a relatively small effect size (*d* = 0.28) was observed in a Cochrane review of intervention studies promoting physical activity among generally healthy people [92]. Similarly, remote interventions such as telephone-based, app-based, and Internet-based coaching versus a control group were associated with rather small effect sizes for change in physical activity (*d* = 0.20) [93]. Given these observations, we assume a small-to-moderate effect of our intervention on the primary outcome (*d* = 0.30). Accordingly, the optimal sample size to detect a significant effect at follow-up is 278 participants (two independent groups, one-tailed, α-error probability = 0.05, power = 0.80). With 20% expected dropouts from baseline to follow-up [94], the targeted sample size is *N* = 334 (IG, *n* = 167: PCG, *n* = 167). This means that every centre will recruit approximately 40 participants per year (*n* = 20 in the IG, *n* = 20 in the PCG). Dependent on the size of the clinics, this corresponds to a recruitment rate of 20–25% of the patients. Enrolment will be systematically monitored by the sponsor-investigator in order to recruit a sufficient number of participants within the planned timeframe.

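### The printed MPA and VPA cut-points for the primary outcome overlap over 5275–5723 counts/min, so they cannot both be right

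*Protocol article*

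**What the plan says.** Under Data assessment the protocol article states: "The primary outcome is objectively assessed physical activity (Actigraph wGT3x-BT monitor, 7 days". The scoring rule is under Primary outcome, Objective physical activity. It defines two intensity categories by accelerometer counts: "moderate physical activity (MPA; 1952–5723 counts per minute", with an energy cost above 3 MET, and "vigorous physical activity (VPA; > 5274 counts per minute, > 6 MET". Daily time in each "is determined based on the raw accelerometer counts and the ActiLife® computer software, with cut-off values derived from" a single published set. On recording it says: "The sampling epoch will be set at 10 s". Activity done without the monitor is added back: "Physical activities listed on the non-wear time sheet will be included as moderate-to-vigorous physical activities".

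The same section uses 150 minutes per week of moderate-to-vigorous activity as its benchmark. It does not state a rule for adding MPA and VPA, or a rule for an epoch that meets both definitions.

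**The concern.** Two adjacent intensity categories from one cut-point set should not share any values. Here the top of the moderate range is higher than the start of the vigorous range, so a band of counts belongs to both. These numbers are the scoring thresholds of the primary outcome, on which the sample size rests ("we assume a small-to-moderate effect of our intervention on the primary outcome"). They are not background text.

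If the printed values were programmed as they stand, three things could follow:

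- Minutes in the band would be counted twice in any total formed by adding MPA and VPA.
- One of the two categories would be too large if they were reported separately.
- Two analysts resolving the conflict in opposite ways would obtain different MPA and VPA minutes from the same recordings.

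**Working it through.** **Inputs**, all from Primary outcome, Objective physical activity: MPA 1952–5723 counts/min; VPA above 5274 counts/min with no upper limit; 10-second epochs. The cut-points are stated directly, so the plan has no derived figure to reproduce.

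**Overlap on the per-minute scale**
- Values meeting both definitions: 5275 to 5723.
- Number of whole values: 5723 − 5274 = 449.
- Whole values in the printed MPA range: 5723 − 1952 + 1 = 3772.
- Share: 449 / 3772 = 11.9%.

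**Overlap on 10-second epochs** (assuming the epoch count is multiplied by 6 to compare it with a per-minute cut-point)
- MPA epochs: 326 (326 × 6 = 1956) to 953 (953 × 6 = 5718), which is 628 values.
- Those also above 5274: 880 (880 × 6 = 5280) to 953, which is 74 values.
- Share: 74 / 628 = 11.8%. The shorter epoch does not remove the overlap.

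**Can the text resolve it?** The MET limits do not help: MPA is given only as above 3 MET, with no upper limit, so it also contains everything above 6 MET. No other section repeats the cut-points. The digits suggest a slip but not its direction. Swapping the middle digits of 5274 gives 5724, one above 5723. Swapping those of 5723 gives 5273, one below 5274. Either figure could be the misprint.

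**With one shared boundary**
- MPA 1952–5723 and VPA above 5723: overlap 0.
- MPA 1952–5274 and VPA above 5274: overlap 0.

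**Consequence of applying the rule as printed**

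| Use of the categories | If 5723 is right | If 5274 is right |
|---|---|---|
| MPA reported alone | correct | too high |
| VPA reported alone | too high | correct |
| MPA + VPA added | band counted twice | band counted twice |
| All time at or above 1952 | unaffected | unaffected |

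**Size if the two are added.** Let s be the share of true MVPA time that falls in the band. The sum is then the true time × (1 + s). The documents do not give s, so these values are assumptions, shown for an illustrative true 30 min/day:
- s = 1%: 30 × 1.01 = 30.3 min/day
- s = 5%: 30 × 1.05 = 31.5 min/day
- s = 10%: 30 × 1.10 = 33.0 min/day

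**The case against.** The strongest reply is that this is a misprint in a condensed article and not a scoring error. The article says the scoring is done in ActiLife with a published cut-point set, and nothing shows that the overlapping values were entered there. A reader might infer that the trial's data have been double-counted; the documents do not support that. This part of the reply stands. It does not make the printed rule usable, because the article gives the thresholds and gives them inconsistently.

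The reply also holds on three further points.

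- **The effect on the primary variable is conditional.** Double counting needs MPA and VPA to be added from overlapping ranges, and no such rule is stated. The 150-minute benchmark and the treatment of non-wear activities both point towards combined MVPA, which need not use the upper boundary at all.
- **The 11.9% is a share of the count scale, not of minutes.** Participants are selected for reporting under 150 minutes of MVPA per week (Criteria for inclusion/exclusion), and the band lies at the upper end of the moderate range. Little time is likely to fall there, although the documents give no figure. The same rule would apply in both arms, so it would not by itself create a difference between arms with the same activity pattern.
- **Separate primary tests are not planned in the text.** Because the section names time in MPA and time in VPA, a reader might infer two primary tests and an inflated type I error. No section says the two will be tested separately. The article names one primary outcome, and the exact summary variable can properly be left to a fuller document.

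**Conclusion.** The point holds as an internal contradiction in the primary outcome's scoring thresholds. The overlap of 449 count values (5275–5723 counts/min) is certain from the text, and the article offers no way to resolve it. Which figure is wrong cannot be told from the document, so it would be too strong to say that VPA in particular is inflated: that is true only if 5723 is the correct boundary. If 5274 is correct, MPA is inflated instead.

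Harm to the primary analysis is possible but not shown. It requires both that the overlapping values are in the software and that the analysis uses MPA, VPA or their sum, and not all time at or above 1952 counts/min. Even then the effect is probably small in this population; the 30.3 to 33.0 min/day range rests entirely on assumed shares. This is a necessary correction that costs little, and it gives no reason to doubt the design.

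**What to change.** 1. Check both figures against the cited cut-point source and print one shared boundary. Say which category takes a value exactly on it, so that every count from 1952 upwards falls in exactly one category.
2. Verify the cut-point settings in the ActiLife installations already in use. Recruitment began in January 2019, and participants receive a profile of their activity level after each assessment (Measures), so this should be done promptly. If the overlapping values were entered, rescore the affected recordings.
3. If combined MVPA is the primary variable, compute it as all valid wear time at or above 1952 counts/min plus the non-wear-sheet activities the protocol already includes. It then does not depend on the disputed boundary. Leaving out the non-wear activities would change the outcome as the article describes it.

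The cost is one corrected number, one clarifying sentence and one settings check. No new data are needed, and the sample size is unaffected.
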